### Data management

Data will be collected in an electronic data management system (Kobotoolbox) and extracted for statistical analysis. One research assistant will be responsible for data management. He will check the data quality during and after data collection in addition to cleaning the data. Additionally, session attendance will be weekly recorded by the CBS facilitators. All information will be stored in a password-protected computer.

### Confidentiality

Data will be collected in an electronic data management system (Kobotoolbox) and extracted for statistical analysis. A file containing all evaluation-related documents (attendance lists, ID logs, informed consent forms, etc.) will be kept in a secure location at the field for the entire duration of the project. In short, data collected for this study will remain confidential and accessible only to the research team. All information will be stored in a password-protected computer.

### Data collection

A team of 20 data collectors will be recruited and given a 3-day training on evaluation objectives, the content of the questionnaire, and electronic data capture, followed by practical sessions to ensure accurate, reliable, and consistent data collection. Quantitative data will be collected in an electronic data management system (Kobotoolbox) and extracted for statistical analysis. A file containing all evaluation-related documents (attendance lists, ID logs, informed consent forms, etc.) will be kept in a secure location at the field for the entire duration of the project. In addition to standardized questionnaires on mental health and psychosocial well-being, several questions related to everyday life like trust, care, respect, safety, responsibility, perceived social support, traumatic events, PTSD, and attributed dignity will be asked. The interviews will take about 45 min.

### Statistical methods

#### Baseline characteristics

Baseline characteristics, both at the cluster (i.e., group size, group location) and individual levels (age, sex, marital status, location, education, occupation and social category), will be cross-tabulated according to the allocated group to check for appropriate balance and to provide an overview of the study population. The baseline characteristics of each group will be summarized as the mean, standard deviation, and range for continuous, approximately normally distributed variables; medians, interquartile range, and range for continuous, skewed variables; and frequencies and percentages of individuals in each category for categorical variables. The formal statistical comparison at the baseline of randomized groups will not be undertaken.

#### Primary analysis

The primary analysis will be performed following an intention-to-treat analysis. Primary outcome measures will be the post-intervention continuous total score of the social dignity questionnaire and its subscales based on socio-therapy phases. As the researchers are interested in discussing change and the correlates of change [42], the primary analysis will compare intervention vs control groups on their mean change in social dignity between baseline and endline, and between baseline and endline2 separately. To counter the problems associated with their use, the baseline scores will be incorporated into the model as a control [42, 43]. The mean change scores in social dignity will be incorporated into the GEE model as a dependent outcome. GEE will help to adequately account for intra-cluster correlation by incorporating in the model the random CBS groups/cluster-specific effect. Our primary interest is at the individual level and the CBS groups/cluster level will be regarded as a nuisance that must be considered for valid inferences [44].

Allocated groups (control versus intervention) will be regarded as fixed effects while clusters and time points are regarded as random effects in the model. With this approach, we will be able to separately model the mean response at the individual level and the cluster within-cluster association. The model will be adjusted using pre-defined covariates. Our primary interest is at the individual level, and the cluster level is regarded as a nuisance that must be considered for valid inference. We will test the robustness of the results by repeating the analyses using mixed random effects regression analysis to compare the two groups and a standard *t*-test to compare the means of the outcomes at the individual level [45, 46]. The estimated difference in mean change from baseline to endline and the corresponding 95% confidence interval (CI) will be presented. Secondary outcomes will be analyzed using the same method as the primary outcome.

Notably, no formal interim analysis will be conducted on the primary and secondary outcomes because we do not have the design issues, anticipated harm, or early intervention effects for the respondent which are the most cited reasons for interim testing [12, 47]. A pool of previous qualitative studies has proven that CBS is a well-established intervention with a well-predefined number of required sessions [19]. As such, no risk or inconvenience was found to be associated with CBS. The participation rate will be captured as usual intervention monitoring exercise to estimate its covariation effects. However, data monitoring will be done by UR team to ensure that the data collected are in the right format at baseline and both end-lines.

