#### Intervention description

The Community-Based Sociotherapy (CBS) intervention is one of the programs initiated in Rwanda to address the psychosocial needs of the Rwandan population in the aftermath of the 1994 genocide against the Tutsi and to restore the social fabric. CBS is a psychosocial peacebuilding intervention that has been shown to promote social cohesiveness, psychological well-being, reconciliation, and economic development among the populations of Rwanda [8, 19]. CBS is also evidenced in other conflict/post-conflict settings, including in the Democratic Republic of Congo [20] and Liberia [8].

In CBS, a group of 10 to 15 people gather in a circle to discuss their daily life problems and psychosocial distress, which turn out to often be related to their past and how it has affected their psychosocial health. The intervention is built on six consecutive phases, each focusing on a specific theme: safety, trust, care, respect, new life orientation, and memories. Throughout these phases, the following principles are applied: interest, equality, democracy, here and now, responsibility, active participation, and learning by doing [18] (see Fig. 1). In the sessions, the sociotherapy facilitators include exercises and cultural games and expressions, which contribute to cohesive group dynamics.

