### Outcomes

#### Primary outcome measure

Following extensive qualitative work with the CBS experts, we defined the impact of the CBS intervention in an itemized way. After we searched the literature for concepts that relate to the lists of items and through iterative feedback working loops between CBS experts and the literature, we came up with a contextually developed definition of social dignity, which CBS experts recognized as an ecologically valid primary outcome measure for CBS.

All items of the self-designed social dignity scale will be summed up to form a total score that will be used to estimate the primary outcome before and after the CBS intervention (baseline, endline1, and endline2). Each item is scored on a 5-point Likert Scale ranging from 1 (never) to 5 (always). We believe that this sum will give a valid measure of social dignity, as qualitative work preceding the trial did not indicate that we should weigh any item of the questionnaire higher than the other.

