### Sample size

The sample size was estimated based on pilot study results. As there was no similar previous study allowing to asses intraclass correlation, the authors of this study have conducted a pilot study on a sample of 559 people. The objectives of the pilot study were (1) to test the psychometric properties of the Social Dignity Scale and (2) to assess potential Intra-CBS groups correlation. The results from the pilot study revealed an intraclass correlation of 0.15. The targeted treatment effects were established in terms of clinical judgment, not through the pilot of data [37]. According to previous CBS experience, an average of 3 out of 15 participants in a CBS group dropout the intervention without achieving at least 11/15 required sessions. All enrolled CBS groups are facilitated to the end of the intervention. Considering an intraclass correlation coefficient, Rho = 0.15 and a standard Alpha = 0.05, an a priori power calculation using the Optimal Design Software [38] revealed that 80 CBS groups (40 control and 40 intervention) composed of 12 participants each group would make it possible to achieve the standard power of 0.80 while detecting a small Cohen’s *d* effect size of 0.3. The required total sample was then found to be 960 (i.e., 12 × 80) participants. However, assuming a minimalistic response rate of 96% according to a previous similar social study in Rwanda evidencing that it ranges from 96% [39] to 99.8% [40], we would need to recruit 1000 participants. To provide a buffer against potential attrition-related problems, at least 15 recruited beneficiaries of CBS that fulfil the inclusion criteria will be included in the study making the final sample size to recruit up to 1200 participants.

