#### Subgroup analysis

Exploratory subgroup analyses of the following possible interactions will be undertaken to assess whether the effect of sociotherapy intervention is modified by the prespecified covariates: survivors, perpetrators, and youth. These subgroup analyses will be performed by adding the interaction term between the allocated group and the subgroup variable into the generalized effect model. Given the limited power to detect treatment–subgroup interactions, analyses of the results will be interpreted with caution. All subgroups will be analyzed using the intention to treat the population. Wherever applicable, to compensate for multiple comparisons, this study will employ a Bonferroni correction factor.

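### The primary analysis names the total score and its phase subscales as primary outcomes at two endlines, but the outcomes section names only the total and the sample size covers a single test at 0.05

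*Protocol article*

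**What the plan says.** Four places in the protocol article bear on this.

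- *Primary outcome measure* (under Outcomes) describes one measure. The items of the social dignity scale are "summed up to form a total score that will be used to estimate the primary outcome".
- *Primary analysis* (under Statistical methods) uses the plural: "Primary outcome measures will be the post-intervention continuous total score of the social dignity questionnaire and its subscales based on socio-therapy phases". It then compares the arms on "mean change in social dignity between baseline and endline, and between baseline and endline2 separately". The section gives no order among these comparisons.
- *Sample size* uses one undivided significance level, "Rho = 0.15 and a standard Alpha = 0.05", with 40 + 40 groups of 12, d = 0.3 and power 0.80.
- *Subgroup analysis* closes with the only remark on multiplicity. Where applicable, "to compensate for multiple comparisons, this study will employ a Bonferroni correction factor". It does not say which tests form the family.

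The number of subscales is not given. The Primary analysis section ties them to the sociotherapy phases, and *Intervention description* counts six: "The intervention is built on six consecutive phases, each focusing on a specific theme: safety, trust, care, respect, new life orientation, and memories".

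**The concern.** Two sections of the same document define the primary outcome differently, and the wider definition does not match the sample size. Under the narrower definition there are two primary comparisons (the total at each endline). Under the wider one there are two for the total plus two for every subscale. The power calculation fits neither, because it describes one test at the full 0.05.

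What is at stake is the meaning of a headline result. If the primary tests are left uncorrected and any of them can carry the claim, the error rate is above 5%. If they are corrected by Bonferroni, the alpha behind the stated 0.80 no longer applies. The scale is self-designed and the Randomization section expects blinding to fail at endline, so emphasis chosen afterwards on one phase or one endline would be hard to defend.

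**Working it through.** **Inputs.** From *Sample size*: 80 groups (40 per arm), 12 per group, ICC 0.15, alpha 0.05, d = 0.3, power 0.80, and recruitment of 15 per group (1200 in all). From *Primary analysis*: two endlines. Assumed, because the documents do not give them: four or six subscales (six would be one per phase), subscale and time correlations from 0.3 to 0.9, and two-sided testing.

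**1. Reproduce the plan's figure.**
- Design effect = 1 + (12 − 1) × 0.15 = 2.65.
- SE of the standardised difference = √(4 × 2.65 / 960) = 0.1051.
- Noncentrality = 0.3 / 0.1051 = 2.855.
- Cluster-level t-test with 80 − 2 = 78 df, two-sided 0.05: power **0.805**. The normal approximation gives 0.815. One-sided 0.05 gives 0.88 and does not match.

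The stated 0.80 is therefore the power of one two-sided test at the full 0.05.

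**2. Count the primary tests.** Tests = (1 total + number of subscales) × 2 endlines.
- Total only: 2.
- Four subscales: (1 + 4) × 2 = 10.
- Six subscales: (1 + 6) × 2 = 14.

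**3. Chance of at least one false positive, uncorrected, if any positive test counts.** Simulated with multivariate normal test statistics, equicorrelated subscales, the total as their sum, and a common correlation between the two endlines.

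| Tests | Correlations 0.9 (subscales and time) | Correlations 0.3 (subscales and time) |
|---|---|---|
| 2 (total only; time correlation only) | 7% | 9.5% |
| 10 (four subscales) | 13% | 32% |
| 14 (six subscales) | 15% | 42% |

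For the total alone the ceiling is 1 − 0.95² = 9.75%.

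**4. Power at d = 0.3 if Bonferroni covers the primary tests.** Same formula with alpha divided by the number of tests and no credit for baseline adjustment. At 15 per group the design effect is 1 + 14 × 0.15 = 3.10 and SE = √(4 × 3.10 / 1200) = 0.1017.

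| Tests | Alpha per test | Power, 12 per group | Power, 15 per group |
|---|---|---|---|
| 1 | 0.05 | 0.805 | 0.83 |
| 2 | 0.025 | 0.71 | 0.75 |
| 10 | 0.005 | 0.49 | 0.53 |
| 14 | 0.00357 | 0.45 | 0.48 |

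**5. What baseline adjustment might return.** The model includes baseline scores. If baseline and endline correlate at r, take the SE as multiplied by √(1 − r²). With r assumed at 0.3 to 0.5:
- two tests: 0.76–0.84 at 12 per group and 0.79–0.87 at 15;
- 14 tests: 0.50–0.66 across 12 to 15 per group.

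The documents give no value of r, and the sample size takes no credit for one.

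**The case against.** The strongest reply is that the article as a whole treats social dignity as one outcome. The abstract names a single scale, there is one objective and one hypothesis for social dignity, and *Primary outcome measure* defines one total. Even within *Primary analysis*, the sentence on the comparison speaks of change in social dignity and does not mention each subscale. On that reading the total leads, there are two tests, and the excess error is modest. This largely stands, and it is why the 7–10% figure comes first. It does not remove the point, because the plural sentence is still there and the two endlines are still unranked.

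A reader might infer something stronger: that CBS can be declared effective on any of 14 tests, with a false-positive chance near 51% (1 − 0.95¹⁴). The documents do not support that. They state neither the number of subscales nor a rule that one positive test suffices. The 51% figure needs independent tests, which is impossible when the total is the sum of the subscales.

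A reader might also infer that the 0.80 power is necessarily lost. For two tests this is not established, since baseline adjustment at a plausible r could restore it. For 14 tests a shortfall remains over the range of r tried.

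It can also be said that a correction is already stated. The Bonferroni sentence is worded for the whole study but sits under Subgroup analysis and names no family of tests. Reading it as covering the primary tests exchanges the error problem for the power problem.

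Finally, a separate analysis plan may set the hierarchy. That is fair for a missing hierarchy, which is not itself the finding. The finding is that the published text states two different primary outcomes, and that its sample size matches one test.

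**Conclusion.** The point holds as a contradiction between two sections and a mismatch with the sample size. *Primary analysis* makes the total and its phase subscales primary at two endlines, *Primary outcome measure* makes only the total primary, and *Sample size* covers one two-sided test at 0.05 (0.805 reproduced).

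Its size depends on matters the article leaves open. Uncorrected, and only if any positive primary test counts as success, the error rate is about 7–10% for the total at two endlines and about 13–42% assuming four to six subscales with correlations of 0.9 down to 0.3. With Bonferroni over the primary tests and no credit for baseline adjustment, power at d = 0.3 is about 0.71–0.75 for two tests and about 0.45–0.53 for 10 to 14. Baseline adjustment may recover some of this by an amount the documents do not allow one to state.

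**What to change.** - In *Primary analysis*, make the total social dignity score at one named endline the single primary test, two-sided at 0.05.
- Test the total at the other endline only if the first test is significant. This fixed sequence keeps the overall error rate at 0.05 and leaves the stated 0.80 intact for the first test.
- Move the phase subscales to secondary outcomes, reported as estimates with confidence intervals.
- Align *Primary outcome measure* with *Primary analysis*, and say which tests the Bonferroni sentence covers.

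Other multiplicity procedures are legitimate, but one that divides alpha would require the power to be recalculated at the alpha actually used. By the normal approximation with 12 per group, Bonferroni needs about 94 groups for two tests and about 132 to 140 for 10 to 14, against the 80 planned.

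The recommended change is wording only and adds no participants. The small downside is that no primary claim can rest on a subscale or on the second endline alone. It should be made before endline data are examined by arm.

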### Plans to promote participant retention and complete follow-up

No additional strategies will take place to improve retention and completion by participants in this trial, in keeping with the ecological design of this study.

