## Methods in analysis to handle protocol non-adherence and any statistical methods to handle missing data

The reasons for missing data will be reported and if missing data is < 5%, multiple imputation will be used to handle missing data [48] using SPSS (version 28).

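### Endline 2 is analysed separately from endline 1, so selective loss between the surveys can bias it, although endline 1 scores that could reduce this are collected

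*Protocol article*

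**What the plan says.** The Primary analysis section compares the arms on "mean change in social dignity between baseline and endline, and between baseline and endline2 separately". On the model it says that "The mean change scores in social dignity will be incorporated into the GEE model as a dependent outcome" and that "the baseline scores will be incorporated into the model as a control". No other score is named as a control.

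The next paragraph of that section says that "clusters and time points are regarded as random effects in the model". Robustness is to be tested by "repeating the analyses using mixed random effects regression analysis to compare the two groups", without saying whether that model covers both endlines together.

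The Primary outcome measure section has social dignity measured at baseline, endline 1 and endline 2. The missing-data section says that "if missing data is < 5%, multiple imputation will be used to handle missing data". It gives no method for 5% or more. On retention: "No additional strategies will take place to improve retention and completion by participants in this trial". The Sample size section assumes a 96% response rate and notes that "an average of 3 out of 15 participants in a CBS group dropout the intervention", meaning that they attend too few sessions.

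**The concern.** Someone seen at endline 1 but not at endline 2 has no change score to endline 2. A separate model therefore gets nothing from that person unless the value is imputed. Among completers, the endline 2 contrast is then valid only if loss is unrelated to the endline 1 score once arm and baseline are known, or if any such relation acts equally in both arms.

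Endline 1 is the nearest earlier measurement, so it may predict both the endline 2 score and who is lost before it. Endline 2 is one of two primary comparisons and the only one that shows whether an effect lasts. Loss that differs by arm is conceivable: by endline participants are expected to know their arm (Randomization section), and controls are promised CBS after the final evaluation (Ethical issues section).

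**Working it through.** **1. The plan's own figure.** The design effect is 1 + (12 - 1) × 0.15 = 2.65. The effective number per arm is 480 / 2.65 = 181.1. Power at d = 0.3 and two-sided alpha 0.05 is 0.815 (normal) or 0.805 (noncentral t, 78 df), against the stated 0.80. The totals also follow: 960 / 0.96 = 1000 and 80 × 15 = 1200. The design reproduces, but it does not model loss between the endlines.

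**2. Inputs the protocol does not give (assumed).** Correlations baseline-endline 1, endline 1-endline 2 and baseline-endline 2: set A 0.5, 0.6, 0.45; set B 0.5, 0.7, 0.5. Loss between the endlines is 4-20% per arm. The log-odds of loss change linearly with the endline 1 score. ICC 0.15 is the protocol's.

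**3. Mechanism.** The weight of endline 1 on endline 2, given baseline, is b = (r12 - r02 × r01) / (1 - r01²), where 0, 1 and 2 stand for baseline, endline 1 and endline 2.
- Set A: (0.6 - 0.45 × 0.5) / 0.75 = 0.50.
- Set B: (0.7 - 0.5 × 0.5) / 0.75 = 0.60.

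The bias is approximately b times the difference between arms in how far selection shifts the baseline-adjusted endline 1 mean among those retained. Equal shifts cancel.

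**4. Size and sign.** Simulation of 480,000 persons in clusters of 12, true effect 0.30 SD at both endlines, slope of 1 per SD where selection is present. Except in the opposite row, low scorers leave. Bias of the separate completer analysis, in SD:

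| Loss CBS / control | Selection on endline 1 | Set A | Set B |
|---|---|---|---|
| 4% / 4% | same in both arms | 0.000 | 0.000 |
| 4% / 4% | CBS only | +0.015 | +0.017 |
| 4% / 4% | control only | -0.014 | -0.017 |
| 10% / 10% | CBS only | +0.036 | +0.042 |
| 20% / 20% | same in both arms | 0.000 | +0.003 |
| 20% / 20% | CBS only | +0.064 | +0.079 |
| 20% / 20% | control only | -0.066 | -0.081 |
| 20% / 20% | opposite (low leave CBS, high leave control) | +0.134 | +0.160 |
| 20% / 4% | same in both arms | +0.051 | +0.062 |
| 4% / 20% | same in both arms | -0.052 | -0.062 |

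Regression imputation by arm from baseline and endline 1 came within 0.003 SD of the full-data estimate in every case.

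**5. At the trial's size.** 80 groups of 15, set A, selective 20% loss in CBS, random 4% loss in control, true effect 0.30, 2500-3000 simulated trials per scenario:

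| Slope per SD | Separate | Using endline 1 | Bias / 0.3 |
|---|---|---|---|
| 0.5 | 0.335 | 0.300 | 0.035 / 0.3 = 12% |
| 1 | 0.365 | 0.300 | 0.065 / 0.3 = 22% |
| 2 | 0.401 | 0.301 | 0.101 / 0.3 = 34% |

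With an SD of the estimate of about 0.09, bias / SD is 0.39, 0.72 and 1.12. Under no effect, Φ(-1.96 + bias/SD) + Φ(-1.96 - bias/SD) gives false-positive rates of about 7%, 11% and 20%.

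At 4% loss in both arms, selective in CBS only, the bias is +0.01 (slope 1) to +0.02 (slope 2).

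**6. Limits of the remedy.** If the same people are lost before endline 1, both analyses are biased alike: +0.04, +0.07 and +0.10 SD. If loss depends on the unseen endline 2 score, using endline 1 corrects only part. If loss is completely random, both are unbiased and the joint standard error is about 1% smaller.

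**7. The mixed model itself.** Fitted once to 400 simulated groups (arm, survey, arm-by-survey, baseline, random group and person), it gave 0.267, against 0.262 with no loss and 0.338 from the separate analysis.

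**The case against.** The strongest reply is that the protocol does not clearly discard endline 1. Random time points make sense only with both endlines in one model, so reporting two contrasts separately need not mean two fits. The planned mixed model might be joint. At the plan's own 4% loss, multiple imputation would apply and could include endline 1; the choice of imputation variables is ordinary analysis-plan content. All this stands, so it is not settled that the scores go unused. What remains is that the section says two incompatible things. A random time effect without an arm-by-survey term would not define the two contrasts in any case, and nothing is stated for 5% missing or more, where the bias would matter most.

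Three stronger inferences are tempting, and the document does not support them.
- *That 20% of CBS members will be missing at endline 2.* The 3 of 15 fall short on sessions. Intention to treat keeps them, and they stop during the 15 weeks, before endline 1.
- *That the separate analysis favours CBS.* The sign follows whichever arm loses its low scorers, and the bias is essentially nil when loss has the same rate and dependence in both arms.
- *That endline 1 scores would cure the problem.* They help only with loss after endline 1 that depends on observed scores.

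It is also fair to say that demoting GEE is not the only adequate repair.

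**Conclusion.** The point holds in conditional form. The conflict between separate analyses and random time points is in the text and needs reconciling. The bias is a possibility, not a certainty: about 0.01-0.02 SD at the plan's 4% loss with selection in one arm, and about 0.04-0.10 SD (12-34% of the target) under an assumed 20% CBS versus 4% control loss. Selection in opposite directions at 20% loss in both arms would give more (0.13-0.16 SD). It is nil under random loss or under equal rate and dependence. All these sizes rest on assumed correlations and loss mechanisms. The change is worth making because it uses scores already collected and costs no precision when loss is random.

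**What to change.** In the Primary analysis section, say whether the two endlines share a model, and remove the conflict over time points. State that the endline 2 estimate uses endline 1 scores at any level of missingness, by one of two routes:

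- **One likelihood mixed model for both endlines:** arm, survey, arm-by-survey, baseline and baseline-by-survey as fixed terms, a random CBS group effect, and within-person correlation. Both contrasts are read from it, with GEE as the check.
- **GEE kept as primary,** with multilevel multiple imputation that includes the endline 1 score and is not limited to less than 5% missing.

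Putting both endlines into an unweighted GEE would not be enough in general, because it needs data missing completely at random or a correctly specified working covariance.

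The text should also say that neither route corrects loss before endline 1 or loss that depends on the unseen endline 2 score. The cost is wording, plus slightly more analysis work or a change in which planned model is primary. No new data are needed.

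### One of the two planned robustness checks, an individual-level t-test, ignores the randomised CBS groups and does not hold its 5% error rate

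*Protocol article*

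**What the plan says.** The Randomization section assigns whole CBS groups to the arms in a 1:1 ratio. The Sample size section allows for the resulting correlation: "The results from the pilot study revealed an intraclass correlation of 0.15". It carries that value into the power calculation with alpha 0.05 ("Considering an intraclass correlation coefficient, Rho = 0.15 and a standard Alpha = 0.05") for "80 CBS groups (40 control and 40 intervention) composed of 12 participants each group". Recruitment is then raised to 15 per group, 1200 in all.

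The Primary analysis section specifies a GEE on the change in social dignity, with the baseline score as a covariate, and says of the groups that "the cluster level is regarded as a nuisance that must be considered for valid inference". The next sentence sets out two robustness checks. The first is a model: "We will test the robustness of the results by repeating the analyses using mixed random effects regression analysis to compare the two groups". The second is "a standard *t*-test to compare the means of the outcomes at the individual level". Nothing in the section gives the t-test a cluster term, a design-effect correction, cluster-robust errors or group means as the unit of analysis.

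**The concern.** When groups are randomised and members of a group resemble each other, the difference between arms varies more from trial to trial than a comparison of independent people would suggest. A standard t-test on individuals leaves out that extra variation. Its standard error is too small, its p-values are too small and its intervals are too narrow.

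A robustness check should be able to expose a fragile main result. This one targets broadly the same difference as the GEE with an understated standard error, so its agreement with a positive GEE result adds little assurance. If it is significant and the GEE is not, the disagreement cannot be interpreted, because ignored clustering alone could produce it. The choice also conflicts with the sentence just before it. It is a stated method, not a detail that could be waiting in an analysis plan.

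**Working it through.** **Inputs.** All are from the Sample size section unless marked.
- Groups: J = 80, 40 per arm.
- Group size: m = 12 in the power calculation, m = 15 as recruited.
- Intraclass correlation: ρ = 0.15, from the pilot of 559 people.
- Effect size d = 0.3, alpha 0.05, power 0.80.
- Assumption: the test is two-sided. The protocol does not state sidedness, but two-sided reproduces its power.
- Assumption: ρ for the analysed change scores equals the pilot ρ. This is varied below.

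**Step 1. Reproduce the plan's own figure.** For a two-arm cluster trial, power follows a noncentral F with 1 and J − 2 = 78 df and

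λ = J·d² / {4·[ρ + (1 − ρ)/m]} = 80 × 0.09 / {4 × [0.15 + 0.85/12]} = 7.2 / 0.8833 = 8.15.

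This gives power 0.805, and 80 is the smallest even number of groups that reaches 0.80. So 80 groups of 12 (960 people) is confirmed, and 960/0.96 = 1000 matches the inflated figure. The sample size therefore handles the groups properly; the t-test does not.

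**Step 2. Design effect.** DE = 1 + (m − 1)ρ.
- m = 12: 1 + 11 × 0.15 = 2.65
- m = 15: 1 + 14 × 0.15 = 3.10

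The true standard error exceeds the one the t-test uses by √DE, a factor of 1.63 (m = 12) or 1.76 (m = 15).

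**Step 3. Actual type I error.** α = 2 × [1 − Φ(1.96/√DE)].
- m = 12: 1.96/1.628 = 1.204, so α = 0.229 and interval coverage is 0.771
- m = 15: 1.96/1.761 = 1.113, so α = 0.266 and interval coverage is 0.734

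Simulating the individual-level t-test under no effect (80 groups, 40,000 replicates) gave 0.226 and 0.266.

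**Step 4. If the correlation in change scores differs from 0.15.**

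| ICC | Error, 12 per group | Error, 15 per group |
|---|---|---|
| 0.01 | 6.3% | 6.6% |
| 0.05 | 11.5% | 13.3% |
| 0.10 | 17.6% | 20.6% |
| 0.15 | 22.9% | 26.6% |

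A further case: suppose only the intervention groups are correlated, at 0.15, with equal total variance in both arms. The average design effect is (2.65 + 1)/2 = 1.83 or (3.10 + 1)/2 = 2.05, and the error is about 15% or 17%.

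Since DE exceeds 1 whenever ρ is positive, the error exceeds 5% for any positive correlation. Only its size depends on the assumption.

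**The case against.** The strongest reply is that the t-test is a supporting analysis with no decision role. The GEE is primary, the sample size allows for clustering, and the mixed model is also planned. Nothing says that significance on the t-test can establish or rescue the main result. This stands, and it limits the harm.

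Four stronger readings are tempting, and the document does not support them.
- *That the trial has no valid robustness check.* The mixed-effects regression is named first and can account for the groups.
- *That 23% to 27% is the false-positive rate of the trial's conclusion.* It is the error rate of one supporting test. The GEE is specified to allow for clustering.
- *That every secondary outcome is affected.* The section says these will use the same method as the primary outcome, which may mean only the GEE. The problem carries over only if the checks are repeated for them.
- *That the t-test will contradict a correct null result or will echo a false positive.* It can do either. Even at an ICC of 0.15 it is non-significant in 73% to 77% of null trials. The GEE adjusts for baseline and covariates, so the two point estimates need not coincide.

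It is also fair to say that the pilot correlation is not stated to apply to change from baseline. That makes the headline size conditional but does not alter its direction. The section cites references for these checks, which were not available here. A citation would not remove the conflict with the section's own requirement on clustering.

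**Conclusion.** The point holds for one of the two robustness checks. As written, the individual-level t-test leaves out the unit of randomisation and contradicts the section's own condition for valid inference. The size of 23% to 27% rests on a two-sided test, equal group sizes and a correlation of 0.15 in the change scores; with lower correlations the inflation shrinks but does not vanish. The consequence is unreliable corroboration, not a wrong primary test. It is a clear error that is easily put right, and it ranks below faults that would touch the primary analysis.

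**What to change.** Replace the individual-level t-test with a cluster-level one: compute one mean baseline-adjusted change per CBS group and compare the 40 intervention means with the 40 control means on 80 − 2 = 78 df. Deleting the t-test would also remove the fault. In either case keep the mixed model as a robustness check and state that it includes a random CBS-group effect. If the checks are meant to extend to secondary outcomes, say so and apply the same change there.

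This is a one-sentence edit that needs no new data and no change to the design or sample size. The cost is wider intervals from this check, by roughly the factor of 1.63 to 1.76 if the correlation is 0.15.
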